### Data collection and management

All participants receive study information through a visual informed consent, using visual elements to explain the procedures, risks, and benefits of study participation, thereby enhancing understanding and communication. Additionally, they receive a written information letter, after which they are requested to provide permission by signing an informed consent form. Measurements are taken through semi-structured interviews, physical measurements, and online questionnaires at start (T0), and after 3 (T1), 12 (T2) and 24 months (T3).

For GOAL! participants, data collection will be conducted by the lifestyle coach and the research team. As this research follows innovative care, lifestyle coaches assess lifestyle behavior, physical health outcomes, and lifestyle goals at all four assessment points (T0-T3). This is part of the program but will also be utilized for research purposes. Lifestyle coaches will record examination results on hard-copy documents, which will then be transferred and securely stored by the research team. Trained researchers and research assistants administer additional questionnaires and measurements. These include psychiatric symptoms, quality of life, and eating behavior at all four assessment points (T0-T3), and healthcare utilization, somatic illness, work, and the implementation process only at the start and end of the program (T0 and T3). Research assistants undergo structured training by experienced research team members in conducting semi-structured interviews via research and interview protocols.

The research team collects all data from the control group. Lifestyle behaviors, physical health outcomes, psychiatric symptoms, and quality of life are evaluated at all four assessment points (T0-T3), whereas healthcare utilization, somatic illness, and work are evaluated only at the start and end of study participation (T0 and T3).

All surveys in this study are entered in, and facilitated by Castor EDC, a cloud-based research data management platform [62]. At T1 and T2, participants have the option to complete some questionnaires via an online survey, thus shortening or obviating the need for an interview with the research team (Table 1). Furthermore, healthcare practitioners and stakeholders receive an online survey regarding the implementation process at the start and the end of the program (T0 and T3). Their informed consent is obtained online.

Participants’ personal information will only be used for measurement purposes and to share general study results, as specified in the consent form. The data will be pseudonymized, personal information will be stored separately, and both will be accessible only to the research team. Access to the data requires two-factor authentication. Data is stored within the institution for 15 years, following national privacy laws, and will not be publicly released.

If participants in the GOAL! program decide to withdraw, they will be asked to remain in the evaluation for additional analysis. If participants withdraw their consent for the evaluation, any data collected prior to withdrawal will be stored in accordance with the data protocol and Dutch law but will not be used for analysis or publication.

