## Methods

### Design and setting

This is a type 1 hybrid quasi-experimental study with a mixed-method matched design. This design allows for the assessment of the effectiveness of GOAL! on health-related outcomes while collecting and analyzing implementation data [41]. An intervention group (*N* = 50) will be compared with a control group (*N* = 50) who continue to receive care as usual and are matched by demographic characteristics. GOAL! is designed in collaboration with stakeholders in multiple municipalities in the Netherlands where GOAL! will be implemented. To avoid contamination, the control group will be recruited in separate municipalities. Due to the nature of the intervention, and the innovative approach to care of this research, randomization or blinding is not possible. Measurements are obtained at start (T0), and after 3 (T1), 12 (T2), and 24 months (T3).

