### Intervention

GOAL! provides multidisciplinary support from registered allied health professionals and peer support workers. In a two-year program, participants receive group-based and individual support on different lifestyle behaviors. The program is divided into the guidance phase (first year), and the maintenance phase (second year) (Fig. 1).

The program starts with an intake session of 60 min conducted by the lifestyle coach, during which lifestyle behaviors, health outcomes, and individual needs are examined. Lifestyle goals are set through shared decision making, a collaborative process proven to enhance effectiveness [42]. In the guidance phase (i.e., year one), the program starts with a 3-month basic course, which encompasses 36 group sessions, each lasting 60 min, guided by allied health professionals. This includes 2-weekly sessions on physical activity (24 sessions in total) and 1-weekly session on nutrition (12 sessions in total). To achieve sustainable lifestyle behavioral change, there is a close collaboration with local stakeholders, thereby facilitating a transfer to the community setting. Thereafter, the aftercare of 9 months starts, with a thematic session of 60 min every two weeks (18 sessions in total) guided by the lifestyle coach about other lifestyle-related topics. These themes can vary based on the needs of the group and include themes such as smoking, sleep, and stress. In the guidance phase, participants receive 8 h of individual support from the lifestyle coach. This coaching can be utilized at the discretion of the participant and is centered around their self-identified lifestyle goals. As the participants’ options, needs and goals evolve, the coaching is adjusted accordingly. Group and individual sessions include theoretical education, interactive elements, assignments, physical activity, and supplementary practical activities (e.g., supermarket visits).

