During the maintenance phase (i.e., second year), there are 3 group sessions of 90 min each, and 5 moments of individual support of 30 min each, both guided by the lifestyle coach. Participants are encouraged to continue their activities in the community setting while the lifestyle coach has a key role in communication and connection with community partners as needed. Following each phase, lifestyle coaches assess and evaluate the changes in lifestyle behaviors and health outcomes together with the participants, setting new goals accordingly through shared-decision making.

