#### Lifestyle behaviors

##### Physical activity and sedentary behavior

The Simple Physical Activity Questionnaire (SIMPAQ) is used to assess physical activity and sedentary behavior. The SIMPAQ consists of 5 items (boxes), averaged over the past 7-day period: time spent in bed overnight (box 1), time sedentary, including napping (box 2), time spent walking (box 3), time spent exercising (box 4) and time spent in incidental activity (box 5). The time spent walking and exercising (boxes 3 and 4) will be combined to calculate the total self-reported moderate-vigorous physical activity time, in hours per week. Alternatively calculating sedentary behavior in hours per day is advised, by subtracting the total non-sedentary behavior (adding boxes 1,3,4 and 5) from 24 h. The SIMPAQ is a reliable and valid tool for assessing physical activity and sedentary behavior in people with SMI [43].

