### Statistical analysis

To assess the effect of GOAL! on lifestyle behaviors and health outcomes, data will be analyzed via multiple linear regressions and linear mixed models (LMMs). LMMs allow for testing the effect over time (four measurement points) and accounting for potential clustering (e.g., participant groups). In all analyses, the treatment condition (GOAL! participants vs. control group, coded as 1/0) will be the independent variable, and the outcomes measures will be the dependent variables, with physical activity (in minutes per week) as the primary outcome. All analyses will be adjusted for potential confounders, such as age (continuous), sex (male vs. female, coded as 0/1), key diagnostic subgroups (categorial, added as dummy variables), baseline values (continuous), session adherence (continuous), and changes in medication use (continuous).

When necessary, missing data will be addressed through multiple imputations via the MICE package in R. When constructing the imputation model, we will include the variables used as predictors in our analysis. The number of imputations and iterations will be based on the proportion of missing data in our LMM. Results from imputed datasets will be pooled using Rubin’s rules.

Implementation factors are processed according to the manual of the measurement instrument. Cost-effectiveness is analyzed in a health-technology assessment.

All analyses will be performed with IBM SPSS statistics 25 and R version 4.04 or higher, based on 95% confidence intervals (*p* < 0.05), and if necessary will be corrected for multiple outcomes (Bonferroni correction).

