Several limitations should be considered within the protocol of this study. First, it is challenging to include people with SMI in intervention research because of illness and healthcare-related complexities. People with SMI often face motivational barriers, self-stigma, psychological complaints, or medication side effects, potentially leading to low enrollment, low adherence, and high dropout rates [33, 34, 66]. Furthermore, healthcare practitioners may encounter inconsistencies in defining who meets the criteria for severe mental illness, organizational barriers (e.g., changes in work practices), and stigma (e.g., negative beliefs and attitudes towards people with SMI, leading to the exclusion of potential participants) [67, 68], which can lead to selection bias.

Second, participants are asked to answer many questions at each measurement point, which can be perceived as burdensome. Some questionnaires may also be difficult to answer or may include sensitive topics. To address these issues, questions can be answered face-to-face or via an online questionnaire, measurements can be spread over multiple sessions, and participants are allowed to skip questions.

Third, for GOAL! participants, half of the questionnaires are administered by the lifestyle coach and the other half by the research team, leading to variability in the data for the outcome measures. However, this is minimized by using as many validated instruments as possible and standardizing measurements and training and consultation throughout the process.

Lastly, the implementation of GOAL! takes place in a select region of the Netherlands, which may limit the generalizability of the findings. In addition, because the control group is recruited in other regions, various contextual factors may influence outcomes. However, this approach helps prevent contamination, and by evaluating the implementation and considering these contextual factors, we aim to gain insights into context-specific barriers, facilitators and processes. This understanding will assist in the interpretation of the outcomes and potential implementation of GOAL! in other regions.

The results of this study will provide a comprehensive understanding of the effectiveness and implementation of GOAL!, serving as essential input for informed decision-making regarding the future integration of lifestyle interventions into outpatient care for people with SMI.

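### The self-reported primary outcome is taken by the lifestyle coach in the GOAL! arm and by the research team in controls, so assessor is aliased with treatment and may bias the primary comparison

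*Protocol article*

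**What the plan says.** The Statistical analysis section names the primary outcome, "with physical activity (in minutes per week) as the primary outcome". The section on physical activity takes it from the SIMPAQ as "total self-reported moderate-vigorous physical activity time".

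Data collection and management assigns the assessors by arm. For GOAL! participants, "lifestyle coaches assess lifestyle behavior, physical health outcomes, and lifestyle goals at all four assessment points (T0-T3"), and these values serve as research data. For the other arm, "The research team collects all data from the control group". Table 1 marks the SIMPAQ, SCOPA-sleep and ASSIST-Lite in the lifestyle-coach column. That block of the table is headed as covering both arms, which does not fit the text for controls. The text is explicit, so I read the column as describing GOAL! participants; table and text should be aligned.

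The coach is also a provider. Under Intervention, the coach holds the intake at which goals are set, leads the aftercare sessions, and in the first year "participants receive 8 h of individual support from the lifestyle coach". The second-year group and individual contacts are "both guided by the lifestyle coach". Design and setting states that "randomization or blinding is not possible".

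The Discussion acknowledges the split within the GOAL! arm: "half of the questionnaires are administered by the lifestyle coach and the other half by the research team, leading to variability". It adds that validated instruments, standardization, training and consultation keep this small.

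**The concern.** A GOAL! participant reports activity to the person who helped set the activity goals and reviews progress on them. A control participant reports to a researcher who has no such role. The outcome is an unblinded self-report, so the answer may depend on who asks, and who asks depends entirely on the arm.

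The Discussion treats the split as added noise within the GOAL! arm. It does not say that the assessor of the primary outcome differs between arms, or that the comparison could be biased. Standardization and training can make the questions uniform; they do not change whom the participant is answering. If reporting to one's coach shifts the answer, part of an observed difference in physical activity would be an assessor effect, and the planned analysis could not show it.

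**Working it through.** **Plan's own figure.** The article gives none for an assessor effect. Its sample size fixes the arm sizes used below. With f² = 0.15, six variables, 5% alpha and 80% power, the overall F test with (6, N − 7) degrees of freedom and noncentrality f²N needs N = 98 (power 0.8035), as stated. The plan then enrols 50 per arm.

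**Can the model separate assessor from arm?** Code treatment 1/0, and assessor 1 for coach, 0 for research team. For every SIMPAQ the two columns are equal, so a design matrix with intercept, treatment and assessor has rank 2 of 3. The listed covariates (age, sex, diagnosis, baseline value, session adherence, medication change) do not include assessor, and adding it would not help. Mixed models and multiple imputation do not alter this.

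**What does baseline adjustment remove?** The coach also assesses T0. Let the coach shift the GOAL! mean by b SD, and let r be the correlation between baseline and follow-up, with equal SDs.

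- Constant shift (b at T0 and at follow-up): change score b − b = 0; baseline as covariate b − rb = (1 − r)b.
- Shift arising wholly after T0 (0 at T0, b at follow-up): b remains under either analysis.

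**False-positive rate.** Assume no true effect, 50 per arm and a two-sided 5% test. With remaining bias d, the rate is Φ(d/SE − 1.96) + Φ(−d/SE − 1.96). Unadjusted SE = √(4/100) = 0.20 SD. With baseline adjustment at r = 0.5, SE = 0.20 × √(1 − 0.25) = 0.173 SD.

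| Assumed shift b | Constant: d = 0.5b | Rate | After T0: d = b | Rate |
|---|---|---|---|---|
| 0.1 SD | 0.05 | 6% | 0.10 | 9% |
| 0.2 SD | 0.10 | 9% | 0.20 | 21% |
| 0.3 SD | 0.15 | 14% | 0.30 | 41% |

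Example: b = 0.2 after T0 gives 0.20/0.173 = 1.155, and Φ(−0.805) + Φ(−3.115) = 0.211.

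**Range over r, for b = 0.2 SD.** At r = 0.3, SE = 0.20 × √0.91 = 0.191: constant d = 0.14 gives 11%, after T0 gives 18%. At r = 0.7, SE = 0.20 × √0.51 = 0.143: constant d = 0.06 gives 7%, after T0 gives 29%.

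**Check.** For a follow-up comparison without baseline adjustment, the same formula gives 7.9%, 17.0% and 32.3% for 0.1, 0.2 and 0.3 SD. A noncentral t with 98 degrees of freedom gives 7.9%, 16.8% and 31.8%.

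**The case against.** **T0 is coach-assessed too.** A reader might infer that any tendency to over-report to the coach passes in full into the treatment effect. The documents do not support that: the primary outcome is a change and baseline values are a covariate, so a constant shift cancels or is reduced to (1 − r) of itself. This objection stands and accounts for the lower set of rates.

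**Growth and direction are not documented.** It is tempting to say that the bias grows with the coaching relationship and favours GOAL!. Both are plausible, but no passage says so. A coach who knows the participant's real activity might restrain over-reporting. Both remain assumptions.

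**Device-measured outcomes.** Coaches also take weight, waist and blood pressure, so one might extend the point to them. The mechanism here is reporting to one's own coach, which does not act on a scale, a tape measure or a monitor. The point is limited to the SIMPAQ and, secondarily, SCOPA-sleep and ASSIST-Lite.

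**Disclosure and practical reasons.** The split is disclosed with mitigation, coach assessment is part of the care programme, and other allied health professionals guide the 3-month course. This is fair, but the coach remains a main provider, and the mitigation addresses consistency of measurement rather than the relationship with the person asking.

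**Online completion.** At T1 and T2 some questionnaires can be done online, which is described as sparing a research-team interview. Nothing says that this covers the coach-collected SIMPAQ, and it does not apply at T0 or T3.

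**Region is confounded with arm anyway.** This is true, and the Discussion admits it. A uniform assessor would not make a positive result unambiguous, but it removes one avoidable alternative explanation.

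**Conclusion.** The point holds in limited form. For the primary outcome, assessor is aliased with treatment by explicit design, and nothing in the planned analysis can separate them. Calling the consequence variability understates it; it is a possible differential bias in the primary comparison.

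The documents do not fix how large it is. At r = 0.5 and assumed shifts of 0.1 to 0.3 SD, the false-positive rate is about 6% to 14% for a constant shift under baseline adjustment, 5% for a constant shift in change scores, and about 9% to 41% for a shift arising wholly after T0. These figures assume no true effect, 50 analysed per arm, equal SDs at both times and no other source of bias. They do not show that a bias exists or which way it runs.

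**What to change.** 1. **GOAL! participants not yet assessed at T0:** the research team administers the SIMPAQ at T0-T3 within its existing contacts for psychiatric symptoms, quality of life and eating behaviour, with the same script and mode as for controls. This is the analysed value. Coaches may keep their own measurement for coaching. Preferably do the same for SCOPA-sleep and ASSIST-Lite.
2. **GOAL! participants whose T0 was coach-collected:** keep the coach series and add a research-team SIMPAQ at the remaining visits, above all T3. Report the T3 comparison with both versions. Do not simply switch assessor. With a coach T0 and a researcher T3, a constant shift b enters as −b in change scores and −rb under baseline adjustment: for b = 0.2 SD and r = 0.5, −0.2 and −0.1 SD.
3. **Sensitivity analysis:** repeat the primary comparison over a stated range of assessor shifts, both constant and arising after T0. Do not correct T0 by a single coach-minus-researcher difference estimated later, since that difference may have changed.
4. **Text:** restate the limitation in the Discussion as possible bias in the primary comparison, and align Table 1 with the text on who assesses controls.

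Cost: a few extra minutes per research contact for a five-item questionnaire, a short call for those who complete T1 or T2 online, and some duplicate questioning in a group for whom the article already lists burden as a limitation. Data collection was under way at submission, with recruitment expected to finish in the first half of 2025, so step 1 may reach few people. T3 comes 24 months after T0, so for late recruits it falls around the first half of 2027, and step 2 may still be feasible for many.

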### Statistical analysis

To assess the effect of GOAL! on lifestyle behaviors and health outcomes, data will be analyzed via multiple linear regressions and linear mixed models (LMMs). LMMs allow for testing the effect over time (four measurement points) and accounting for potential clustering (e.g., participant groups). In all analyses, the treatment condition (GOAL! participants vs. control group, coded as 1/0) will be the independent variable, and the outcomes measures will be the dependent variables, with physical activity (in minutes per week) as the primary outcome. All analyses will be adjusted for potential confounders, such as age (continuous), sex (male vs. female, coded as 0/1), key diagnostic subgroups (categorial, added as dummy variables), baseline values (continuous), session adherence (continuous), and changes in medication use (continuous).

When necessary, missing data will be addressed through multiple imputations via the MICE package in R. When constructing the imputation model, we will include the variables used as predictors in our analysis. The number of imputations and iterations will be based on the proportion of missing data in our LMM. Results from imputed datasets will be pooled using Rubin’s rules.

Implementation factors are processed according to the manual of the measurement instrument. Cost-effectiveness is analyzed in a health-technology assessment.

All analyses will be performed with IBM SPSS statistics 25 and R version 4.04 or higher, based on 95% confidence intervals (*p* < 0.05), and if necessary will be corrected for multiple outcomes (Bonferroni correction).

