#### Healthcare and societal costs

The Treatment Inventory of Costs in Patients with psychiatric disorders (TIC-P) is used for the evaluation of healthcare utilization, medication use, and productivity loss due to health problems. The TIC-P consists of 14 questions to assess healthcare utilization in the past 3 months (e.g., doctor visits, treatment, and medication use), and 11 questions about productivity losses due to health problems (e.g., hindering paid and unpaid work). The costs are calculated by multiplying the quantity of healthcare utilization and productivity loss by the related costs according to national guidelines. The TIC-P is a feasible and reliable instrument for people with mental health problems [59].

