**Intervention and control group**						
T0	Demographic characteristics	Gender	Categorical		x	
		Nationality	-		x	
		Ethnicity	Categorical		x	
		Date of birth (age)	Years		x	
		Diagnosis	Categorical		x	
		Marital status	Categorical		x	
		Highest level of education	Categorical		x	
		Primary source of income	Ratio		x	
T0, T1, T2, T3	Physical activity and sedentary behavior	Simple Physical Activity Questionnaire (SIMPAQ)	Moderate-vigorous physical activity in min/week and sedentary time per day	x		
	Eating behavior	MijnEetmeter	Daily intake of nutrients and daily consumption according to the Dutch ’Wheel of Five’		x	
	Sleep	Scales for Outcomes in Parkinson’s Disease sleep (SCOPA-sleep)	Total scores for nighttime sleep quality and daytime sleepiness	x		
	Substance use	Alcohol, Smoking and Substance Involvement Screening Test Lite (ASSIST-Lite)	Total scores of tobacco, alcohol, cannabis, stimulants, sedatives and opioids and psychoactive use	x		
	Physical health	Weight	kg	x		
		Abdominal circumference	cm	x		
		BMI	kg/m^2^	x		
		Fat percentage	%	x		
		Blood pressure	mmHg	x		
	Psychiatric symptoms	Brief Symptom Inventory (BSI)	Total scores for 9 symptom dimensions: somatization, obsession-compulsion, interpersonal sensitivity, depression, anxiety, hostility, phobic anxiety, paranoid ideation and psychoticism		x	
	Quality of life	Euro-Qol-5D-3 L (EQ-5D-3 L)	Index score based on the Dutch tariff and VAS score		x	
T0, T3	Care and social costs	Treatment Inventory of Costs in Patients with psychiatric disorders (TIC-P)	Healthcare utilization, medication use, productivity loss and costs (€)		x	

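### Change in medication use is a covariate in every analysis, but medication is recorded only at T0 and T3, so no change to T1 or T2 can be observed

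*Protocol article*

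**What the plan says.** The Statistical analysis section plans multiple linear regressions and linear mixed models. Of the latter it says: "LMMs allow for testing the effect over time (four measurement points"). The adjustment applies throughout: "All analyses will be adjusted for potential confounders, such as age (continuous"), and the list ends with "baseline values (continuous), session adherence (continuous), and changes in medication use (continuous").

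Medication use has one stated source. Under Healthcare and societal costs, the TIC-P "is used for the evaluation of healthcare utilization, medication use, and productivity loss due to health problems", through "14 questions to assess healthcare utilization in the past 3 months (e.g., doctor visits, treatment, and medication use").

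Its timing is given three times, consistently:

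- The T0, T3 row of Table 1 lists "Healthcare utilization, medication use, productivity loss and costs" as the TIC-P variables.
- For GOAL! participants, the Data collection and management section has the research team assess "healthcare utilization, somatic illness, work, and the implementation process only at the start and end of the program (T0 and T3").
- For controls, the same section says "whereas healthcare utilization, somatic illness, and work are evaluated only at the start and end of study participation (T0 and T3").

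The primary outcome, physical activity by SIMPAQ, is scheduled at all four visits.

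**The concern.** The covariate list and the visit schedule do not fit together. The main model analyses outcomes at 3, 12 and 24 months, but one of its named covariates can be scored only at 24 months. An analyst following the text has to decide what goes in the T1 and T2 rows, and neither available choice is sound.

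What is at stake is the meaning of the 3- and 12-month treatment effects. A confounder of an outcome must precede it. A medication change that happens after the T1 visit cannot have influenced T1 activity, though T1 activity, or the programme itself, could have influenced the later change. Adjusting an early outcome for such a variable does not remove confounding and may distort the comparison. This matters more in a non-randomised study, where the covariate set carries much of the argument for comparability.

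The mismatch is one of data availability. It is separate from the general question of whether any on-study variable should be adjusted for, and it would remain if that were settled in favour of adjustment.

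**Working it through.** No figure in the plan attaches to this covariate. The nearest one, the sample size of 98, reproduces: an omnibus F test with 6 and 98 − 7 = 91 degrees of freedom and noncentrality 0.15 × 98 = 14.7 has power 0.804 at the 5% level. This point does not affect it.

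**Step 1: schedule against model.** Visit months come from Design and setting. Instrument timing comes from Table 1.

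| Visit | Month | SIMPAQ | TIC-P | Change from T0 observable | Months before T3 |
|---|---|---|---|---|---|
| T0 | 0 | yes | yes | reference | 24 |
| T1 | 3 | yes | no | no | 24 − 3 = 21 |
| T2 | 12 | yes | no | no | 24 − 12 = 12 |
| T3 | 24 | yes | yes | yes | 0 |

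With 50 + 50 participants, 0 of 100 have an observable change at T1 and 0 of 100 at T2.

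**Step 2: other sources.** The article takes the diagnosis from patient records but says nothing similar for medication. The eligibility criteria mention drug treatment for metabolic risk factors, which is an entry check and not a repeated measure. The TIC-P recall of 3 months means that the T3 reading covers about months 21 (24 − 3) to 24. It does not reach back to T1 or T2.

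**Step 3: the two ways to code the covariate.**

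- *Time-varying.* All 200 planned T1 and T2 values are missing by design. MICE needs some observed values of a variable to estimate its distribution, and here there are none.
- *One T0-to-T3 change per person.* This exists for T3 attenders and can be imputed for others. Used in the T1 and T2 rows, it adjusts those outcomes for a quantity completed 21 and 12 months later. Part of the change may have happened before T1 or T2, but two readings cannot show when.

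**Step 4: effect of a missing T3.** The protocol gives no dropout rate, so take 30% missing T3 as an assumption, with T1 and T2 complete. There are then 100 × 3 − 30 = 270 post-baseline records. A complete-case fit with the person-level change keeps 70 × 3 = 210 records from 70 people. With the covariate imputed, all 270 records from 100 people are used. For assumed T3 missingness of 10% to 40%, a complete-case fit would lose up to 2 × 10 = 20 to 2 × 40 = 80 of the 200 T1 and T2 records. With imputation, none is lost for this reason.

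**The case against.** The strongest reply is that the plan already deals with missing covariates. The Statistical analysis section provides for MICE where needed, puts the analysis predictors in the imputation model, and pools by Rubin's rules. A missing T0-to-T3 change is then an ordinary missing predictor. This stands. A reader might infer that everyone who misses T3 also loses their T1 and T2 outcomes, and that the estimated effect is inflated at every visit. The documents do not support that. It would take a decision not to impute, a complete-case fit, and a selective dropout pattern that the article does not state. Step 4 shows that the record loss disappears once the covariate is filled in.

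Two further facts weaken the stronger reading. People who leave GOAL! are to be asked to stay in the evaluation, so leaving the programme is not the same as missing T3. Data from those who withdraw consent for the evaluation are excluded from analysis whatever the covariates are.

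Some risk remains. The article gives no rule for when imputation is needed, and a mixed model handles missing outcomes without it, so an analyst could skip it. The limitations mention potentially high dropout without a rate.

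It can also be said that the covariates are offered as examples and that an article condenses a fuller plan. But this covariate is named, its scope is all analyses, and a fuller analysis plan cannot supply measurements that the schedule does not collect. Imputation answers the missing T3 value only. It does not answer the timing problem.

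**Conclusion.** The point holds as a conflict between the covariate list and the measurement schedule. Medication change is observable at one of three follow-up visits, and for none of the 100 planned participants at T1 or T2. Either coding is defective: one has no data at T1 and T2, and the other adjusts the 3- and 12-month outcomes for information recorded 21 and 12 months later.

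Loss of T1 and T2 records is conditional on the covariate not being imputed and a complete-case fit being used. Any resulting bias or loss of precision depends further on an assumed dropout rate and mechanism, so no fixed figure should be attached to it.

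The conclusion assumes that the TIC-P is the only source of medication data, as the article describes. It does not affect the sample size. A regression of the T3 outcome can at least be run with the T0-to-T3 change. The fault is moderate and worth correcting before analysis, because it concerns a named covariate in the primary model.

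**What to change.** In the Statistical analysis section, replace change in medication use with medication use at T0, both in the mixed model and in any regression of a T1 or T2 outcome. The TIC-P already schedules this reading for both groups. Participants may skip questions, so some T0 values may be missing, but they can be handled by the planned imputation.

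If the T0-to-T3 change is still wanted, confine it to a sensitivity analysis of the T3 outcome and label it as such.

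The cost is about one sentence and no new data. Data collection was still under way when the article was submitted. The small downside is that on-study medication change no longer enters the main model.
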